### Processes, interventions, and comparisons

#### Initial clinical assessment and sample collection/week − 6

During the first visit, consenting participants will be interviewed and examined by the trial doctor and eligibility determined based upon inclusion criteria, medical history, pre-existing conditions, current medications as well as recent travel to worm-endemic countries, known previous worm infections, and deworming treatments. The trial doctor will also conduct a full physical examination during initial screening including height, weight, examination of respiratory, cardiovascular and nervous systems, and a pregnancy test for females. Participants will be asked to attend Sullivan Nicolaides Pathology (SNP) for a fasting blood test assessing lipid profile, liver function, fasting glucose and insulin (Table 2).

**Table 2 Tab2:**
[figure not shown]
Schedule of investigations

BP, blood pressure; HR, heart rate; Temp, temperature; Resp, respiratory rate; HIV, human immunodeficiency virus; HepB & C, hepatitis B and hepatitis C; FBC, full blood count; U & E, urea and electrolytes; CRP, C-reactive protein; PUFA, polyunsaturated fatty acids; Hb1Ac, glycated haemoglobin; LPSBP, lipopolysaccharide-binding protein; UACR, urinary albumin-creatinine ratio; DEXA, dual-energy X-ray absorptiometry; PBMC, peripheral blood mononuclear cells

The study team will contact participants after the screening visit to inform them of their eligibility to proceed. If eligible, the study team will book the next visit according to the study schedule. Clinical assessments will consequently be completed during all follow-up assessments to ensure patient safety and monitoring. Pathology sampling (blood and faeces) will be repeated at intervals throughout follow-up. The schedule of visit requirements is detailed below.

#### Baseline visit/week − 4

During this visit, the study doctor will review the laboratory test results, confirm continued eligibility for participation, perform a full physical examination, and administer diet, health and activity questionnaires, which have been previously validated [20–23]. Blood and faecal samples will be collected and body composition determined via dual-energy X-ray absorptiometry (DEXA) (Table 1). The study doctor will obtain written informed consent for storage of health information and/or blood or tissue samples in the university’s Biobank.

#### Treatment period/week 0 to week 104

The treatment period will last up to 104 weeks during which participants will be required to attend the clinic for two inoculation visits eight weeks apart and four evaluation visits approximately 26 weeks apart. Participants may also have telephone and/or Skype appointments with a designated study team member to monitor their health status and promote retention; these visits will be scheduled with participants by negotiation. At the end of the treatment period, participants will have their final blood and stool tests and DEXA scan, complete the scheduled questionnaires, and undertake an exit consultation and examination with the study doctor. Furthermore, as a mandatory requirement of the study, participants will be provided with the anthelmintic treatment mebendazole (100 mg to be taken twice daily for 3 days to clear the hookworm infection) at no cost to them; however, it is not mandatory for participants to take this medication. Participants electing to refrain from taking the anthelmintic treatment (that is choosing to keep their helminths) following completion of the 104-week period will be advised that their future medical care will be passed onto their general practitioner. At 104 weeks, the study will become unblinded, and there will be an optional 52-week extension to the study for willing participants to examine the impact of de-worming medication on safety, immunological and metabolic parameters.


##### Safety and clinical monitoring

During the initial screening visit and every visit thereafter (or as required in the event of an adverse event), general health assessments, physical examination and vital signs (blood pressure, heart rate, temperature and respiratory rate) will be obtained to ensure safety and monitoring. Urine pregnancy test will be performed for female participants at the beginning of the study (positive tests exclude the participant from the trial) and urinary beta human chorionic gonadotropin testing will be performed during the study, if pregnancy is suspected. Should pregnancy occur during the study, the participant will be treated as an Early Termination.

Incidence and severity of adverse events (AEs) and SAEs will be evaluated formally via structured questionnaires (Additional file 3) reviewed by the investigating clinician and informally via participant-initiated contact. The most significant side effects are likely to occur during the first 4–6 weeks following inoculation as the worms anchor themselves to the intestinal mucosa to facilitate feeding and avoid ejection by gut peristalsis [27]. Common side effects during this initial colonisation include abdominal pain, increased flatulence, nausea, and bloating [28]. The second inoculation visit eight weeks after the first inoculation will provide an ideal opportunity to identify/monitor any side effects. Potential side effects have also been outlined in an extensive participant information sheet provided prior to informed consent and are reiterated during the first inoculation visit. Participants are encouraged during the first inoculation visit to contact the trial doctor should they notice any unusual signs and symptoms. If deemed necessary by the trial doctor, participants will be called in for an additional examination, during which they can elect to discontinue with the trial. Should the symptoms be consistent with potential side effects of hookworm infection, the participant may become unblinded and offered anthelmintic medication.

Pathology samples (blood) will be monitored every 6 months for incidence and severity of laboratory abnormalities (Table 2). In the event of a SAE related to the trial, the participant will firstly be referred to their own GP and the case referred to an independent safety committee. With the consent of the participant, their regular GP will be notified routinely of their participation in the study at commencement. This will be in the form of a letter stating the nature of the study, objectives, and concomitant drugs to be avoided; the participant will also receive a copy of this letter.

#### Outcomes

The primary outcome measure will be the safety of experimental hookworm infection of otherwise healthy women and men with 20 *Na* L3 as evaluated by number of reported AEs and SAEs, assessment of general health, and successful completion of the 24-month trial.

Secondary outcomes include:
safety/tolerability of the higher dose of 40 *Na* L3longitudinal and inter-cohort changes in metabolic parameters (HOMA-IR, DEXA, WC, body mass index, fasting insulin and glucose, lipopolysaccharide-binding protein, glycated haemoglobin, blood pressure, resting heart rate, C-reactive protein, adiponectin, full blood count, white blood cell count, omega-3 poly-unsaturated fatty acid profile, urinary albumin-creatinine ratio)immunological parameters (fluctuations in blood and serum Type 1 and Type 2 immune responses)longitudinal and inter-cohort changes in the composition of the faecal microbiomeimpact of de-worming medication on, safety, immunological and metabolic markers

### Data collection, management, and statistical analyses

All eligible participants will be assigned a unique identification number at their first screening visit. Participant confidential data, including anthropometric measures, lifestyle, and medical history, will be recorded on a hardcopy Case Report Form (Additional file 4), which will then be entered into a password protected electronic database developed specifically for this trial. Hard copy Case Report Forms will be stored in participant trial folders in a locked cabinet in a secure environment at the JCU Cairns campus. Access to the folder containing the databases will be restricted to study personnel only, who will have signed a confidentiality agreement as a condition of their involvement in the study. Data from the final trial data set will be provided to investigators and statisticians in de-identified electronic format and this data will be linked to Case Report Form data using the unique identification number, initials, and date of collection. While a data management team was not formed due to minimal risks associated with the study, data will be audited regularly by independent monitors for independent source data verification.

At trial conclusion, each participant will be provided with an individual report including their baseline test results and any changes over the study period. At this time, they will also be informed of study allocation (20 x L3, 40 x L3, placebo). Upon publication of results, the participants can opt to receive a copy of the manuscript.

#### Sample size

This Phase 1b safety and dose-ranging study will include 45 participants with 15 to be infected with 20 x L3, 15 to be infected with 40 x L3, and 15 in the placebo control group. In the absence of other effect size data from human trials upon which to base a power calculation, and as a change in HOMA-IR from Baseline is a primary metabolic outcome of this study, we have adapted the SUGARSPIN HOMA-IR result [29] and assume an effect size of 1.06 over 2 years. A total of 15 participants in each group reflects 80% power to detect an effect size of 1.06 using the T-statistic and 1.023 using Z-statistic. The aim to recruit 54 participants allows for a potential drop-out rate of 20%.

#### Data processing and statistical analyses

##### Safety of infection

The primary outcome, the safety of infection with 20 *Na* L3, will be assessed using a chi-squared test of proportions to determine any differences in the proportions satisfying the safety criteria at 24 months between the placebo, 20 x L3 and 40 x L3 groups. Kaplan Meir models will be used to assess progression throughout the study, and Cox regression models will assess safe progression through the study. Standard descriptive statistics will be performed on all outcome measures at Baseline, all interim points of assessment, and at 24 months after inoculation (categorical variables: absolute and relative frequencies; numerical variables: mean and standard deviation or median and interquartile range, dependent on data distribution). Successful *Na* infection will be confirmed using qPCR detection of parasite eggs in faecal samples taken at Week 26. The faecal sample collected at Baseline (Week -4) will be used for assessment of current or previous helminth infections that could have interfered with trial outcomes.

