	Exclusion criteria: Pregnancy, established chronic disease (CVD, diabetes, cancer, renal, gut disorder), history of substance abuse or current substance abuse, major allergies, known immunodeficiency disorder, asthma, taking prescribed medications or nutritional supplements likely to interfere with study outcomes, inability to provide informed consent.
Study type	Interventional
	Allocation: block randomised; intervention model: parallel assignment; Masking: double-blind, sealed envelopes and containers
	Primary purpose: prevention
	Phase 1
Date of first enrolment	March 2018
Target sample size	45
Recruitment status	Recruiting
Primary outcome(s)	Safety of experimental inoculation with 20 L3, defined by (a) Number of reported adverse events (AEs), relative to placebo cohort, (b) Assessment of general health and (c) Successful completion of 24-month trial. Adverse reactions: including but not limited to abdominal pain, rash, fever, weight loss, fatigue, nausea (mild, moderate or severe as assessed by trial doctor).
Key secondary outcome(s)	Changes in insulin sensitivity from blood pathology taken at each participant contact point during the 24-month trial; Change in BMI measured by any alteration in weight (kg) and height (cm); Change in waist circumference (cm) Change in bacterial richness of microbiome measure by shotgun assay of faecal sample

Hypotheses are that experimental infection with the human hookworm *Na*
will be well-tolerated and safe in this cohort of otherwise healthy but obese women and men.will induce a biased Type 2 and regulatory immune response with concomitant suppression of systemic, pro-inflammatory Type 1 responses.will stabilise or improve determinants of metabolic disease.will modify the composition of the gut microbiota.

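### The primary safety test compares all three groups at once, so it does not isolate the stated primary question, 20 L3 versus placebo

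*Protocol article*

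**What the plan says.** Table 1 of the protocol article gives the primary outcome as "Safety of experimental inoculation with 20 L3", and its first component as "Number of reported adverse events (AEs), relative to placebo cohort". The *Outcomes* section repeats that the primary measure concerns infection with 20 L3, "as evaluated by number of reported AEs and SAEs, assessment of general health, and successful completion of the 24-month trial". It lists "safety/tolerability of the higher dose of 40" L3 among the secondary outcomes.

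The *Safety of infection* section names the same primary outcome and states how it is tested: "assessed using a chi-squared test of proportions to determine any differences in the proportions satisfying the safety criteria at 24 months". The groups entering that single test are all three trial arms: "between the placebo, 20 x L3 and 40 x L3 groups". Kaplan-Meier and Cox models and descriptive statistics follow, again without a named contrast.

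The *Sample size* section plans "15 to be infected with 20 x L3, 15 to be infected with 40 x L3, and 15 in the placebo control group". The only power statement there concerns HOMA-IR: "A total of 15 participants in each group reflects 80% power to detect an effect size of 1.06 using the T-statistic". No figure is given for the safety test.

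**The concern.** The primary question has one active dose and one comparator. The primary test has three groups and two degrees of freedom, and asks whether any of them differs. These are different questions.

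The test can reject because 40 L3 differs, with 20 L3 no different from placebo. It can also fail to reject when 20 L3 does differ from placebo and 40 L3 lies in between. Either way, the headline statement about 20 L3 depends partly on a dose that the protocol ranks as secondary. The first case is not far-fetched on the protocol's own account: the section on randomisation and inoculation says that adverse effects become more troublesome above 25 L3, which lies between the two doses studied.

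**Working it through.** **Inputs.** From the protocol: 15 per group, three groups, Pearson chi-squared test of proportions at 24 months. Assumed: two-sided 5% level and all failure rates, since the protocol gives neither. A failure is a participant who does not satisfy the safety criteria. Triplets are in the order placebo/20 L3/40 L3.

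**1. The protocol's own figure.** It concerns HOMA-IR. For two groups of 15 at 80% power, the z version is (1.960 + 0.842) × √(2/15) = 1.023, and the noncentral t version is 1.060. Both match the *Sample size* section at a two-sided 5% level, which makes that level a reasonable assumption here.

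**2. Rejection driven by 40 L3 alone.** All 16³ possible tables were enumerated, each weighted by three binomial probabilities with n = 15. The probabilities of the tables with p ≤ 0.05 were then summed.

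| True failure rates | 20 L3 minus placebo | Three-group test rejects |
|---|---|---|
| 10/10/30% | 0 | 27% |
| 10/10/40% | 0 | 52% |
| 10/10/50% | 0 | 76% |
| 20/20/40% | 0 | 23% |
| 20/20/70% | 0 | 87% |

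**3. One table of each kind.** With total failures T, expected failures per arm are e = T/3, and X² = Σ(x − e)² × [1/e + 1/(15 − e)]. On 2 df, p = exp(−X²/2).
- Failures 1/1/6: e = 2.667; Σ = 2.778 + 2.778 + 11.111 = 16.667; X² = 16.667 × (0.3750 + 0.0811) = 7.60; p = 0.022. The placebo and 20 L3 arms are identical.
- Failures 1/6/3: e = 3.333; Σ = 5.444 + 7.111 + 0.111 = 12.667; X² = 12.667 × (0.3000 + 0.0857) = 4.886; p = 0.087. The pairwise comparison of 6/15 with 1/15 gives X² = 30 × (6×14 − 1×9)² / (15×15×7×23) = 4.658 on 1 df, uncorrected p = 0.031; Fisher p = 0.080.

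**4. Is the chi-squared approximation sound at 15 per arm?** Expected failures per arm are 15 × the pooled rate. They fall below 5 when that rate is under 1/3; expected non-failures fall below 5 when it is over 2/3. At 20% failing (the protocol's drop-out allowance, used as an illustration because completion is part of the outcome) the count is 15 × 0.20 = 3.0 per arm, so three of the six cells are below 5.

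The exact type I error at nominal 5% is:

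| Common failure rate | 2% | 5% | 10% | 20% | 30% | 50% |
|---|---|---|---|---|---|---|
| Exact size | 0.005 | 0.024 | 0.035 | 0.043 | 0.052 | 0.050 |

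The maximum is about 0.052. Single tables can still mislead: 0/0/3 gives Pearson p = 0.040 against an exact p of 0.096, and 2/2/7 gives 0.049 against 0.069.

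**5. What the direct contrast would show.** Wilson 95% limits are 0.012 to 0.298 for 1/15 and 0.198 to 0.643 for 6/15. The Newcombe interval for 20 L3 minus placebo is then:
- 1/15 vs 1/15: 0 ± √[(0.067 − 0.012)² + (0.298 − 0.067)²], that is −24 to +24 points.
- 6/15 vs 1/15: lower limit 0.333 − √[(0.400 − 0.198)² + (0.298 − 0.067)²] = 0.026; upper limit 0.333 + √[(0.643 − 0.400)² + (0.067 − 0.012)²] = 0.582. That is a difference of 33 points, with limits of 3 and 58.

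For 10% vs 50% failing, the power of the pairwise test is 54% by Fisher and 73% by uncorrected Pearson.

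**The case against.** The strongest reply is that pairwise contrasts and small-sample variants are often left to an analysis plan, and that the planned per-arm frequencies would let a reader see when 40 L3 drives a result. The second half is fair. The first would hold if the article were silent, but it names the primary outcome as 20 L3 and then fixes a three-group test for it.

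A second reply is that the three-group test is not always the less sensitive one. This stands. At 10/50/10% it rejects in 76% of trials and at 10/50/50% in 71%, against 54% for Fisher on 20 L3 versus placebo. Low sensitivity here comes mainly from 15 per arm, and changing the test does not cure that. It is also true that the 76% in step 2 depends on a large assumed 40 L3 effect, which is why a range is shown.

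Some stronger readings are tempting but not supported:
- *The approximation fails at 15 per arm.* The test is conservative at low rates and close to nominal otherwise. Only single sparse-table p-values are in doubt, and the protocol gives no failure rate that settles how sparse the tables will be.
- *A non-significant result would be taken as proof of safety.* No section says so.
- *The outcome is a count and must be modelled as one.* The outcome is a composite of events, general health and completion, and a proportion meeting criteria is a legitimate summary of it. A count model is a preference.
- *A trend test should replace the three-group test.* This too is a preference, and it would be weak if failures did not rise steadily with dose.

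**Conclusion.** The point holds as a mismatch between the stated primary outcome and the test fixed for it. The three-group test does not isolate 20 L3 versus placebo. Under the assumed rates with no 20 L3 effect, it rejects in 23% to 87% of trials because of 40 L3 alone; with 10% failing on placebo and 20 L3, the figures are 27%, 52% and 76% as the 40 L3 rate goes from 30% to 50%. It can also miss a difference that an uncorrected pairwise test would flag, though Fisher would not flag it in the example shown.

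The size of the problem rests on the assumed 5% level, the assumed failure rates and 15 analysed per arm; the mismatch itself rests on the protocol's text alone. The three-group test has no inflated type I error, and sparse tables are a secondary reason to prefer a small-sample method.

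**What to change.** Reword the *Safety of infection* section so that:
- the primary analysis is 20 L3 versus placebo, as the difference in the proportion not satisfying the safety criteria at 24 months, with a 95% confidence interval by a named small-sample method (for example Newcombe);
- a named small-sample test supports the interval;
- 40 L3 versus placebo, and any three-group comparison, are labelled secondary;
- the safety conclusion for 20 L3 is drawn from the interval. This needs saying because interval and test can disagree: for 6/15 vs 1/15 the Newcombe interval excludes zero while Fisher gives p = 0.080.

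The cost is wording only, with no change to sample size or data collection. The downside is a more modest conclusion. Fisher's test has only 54% power for 10% vs 50%, and even identical arms with 1/15 failing each leave an interval of −24 to +24 points.

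### The primary safety outcome is led by a number of adverse events, but the only planned test uses an undefined pass/fail status, so the AE number has no between-group analysis

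*Protocol article*

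**What the plan says.** The Outcomes section states the primary outcome as safety of infection with 20 L3, "as evaluated by number of reported AEs and SAEs, assessment of general health, and successful completion of the 24-month trial". The registration data set (Table 1, in Background) lists the same three components and makes the first explicitly comparative: "Number of reported adverse events (AEs), relative to placebo cohort, (b) Assessment of general health and (c) Successful completion of 24-month trial". Table 1 also says that reactions are graded "mild, moderate or severe as assessed by trial doctor", but attaches no pass mark to any grade.

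Under Data processing and statistical analyses, Safety of infection, the planned analysis of this outcome is made "using a chi-squared test of proportions to determine any differences in the proportions satisfying the safety criteria at 24 months". All three arms enter that comparison. The same paragraph plans Kaplan-Meier models, says that "Cox regression models will assess safe progression through the study", and adds that "Standard descriptive statistics will be performed on all outcome measures at Baseline" and at later time points.

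**The concern.** A test of proportions needs a yes/no status for each participant. The stated outcome supplies a count, an assessment and a completion status, and nothing converts them into that one status. There is no threshold for AE number, severity, relatedness or general health, and no rule for combining the three components.

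Two things are at stake. First, the comparison that Table 1 names, AE number against placebo, is not made by any planned test. Second, the verdict on the trial's main question depends on a rule that could still be chosen after the data are seen. With 15 per arm, different reasonable rules can give different answers, and a non-significant difference in an ill-chosen proportion is easily read as evidence of safety.

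**Working it through.** **The plan's own figure.** The only power statement is 15 per group, 80% power, effect size 1.06 (t) or 1.023 (z), for HOMA-IR. Assuming two-sided alpha 0.05, which is not stated: 1.023 × √(15/2) = 2.80, and 2.80 − 1.96 = 0.84, which is 80% power. The noncentral t at 1.06 also gives 80%. The figure reproduces, but it says nothing about the safety test.

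**What a proportion can show with 15 per arm.** Take 20 L3 against placebo, with 90% against 43.7% meeting the criteria (mean 66.85%).
- Null SE: √(2 × 0.6685 × 0.3315/15) = 0.172.
- Alternative SE: √((0.9 × 0.1 + 0.437 × 0.563)/15) = 0.150.
- (0.463 − 1.96 × 0.172)/0.150 ≈ 0.84, which is 80% power.

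So a gap of about 46 points is needed. For 90% v 70% power is 27%, and for 90% v 60% it is 47%.

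**What dichotomising the count costs.** The document gives no AE rate, so these inputs are assumptions: placebo mean m of 1 to 4 AEs per participant, rate doubled on 20 L3, negative-binomial dispersion α of 0.3 to 1.0, equal follow-up.

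The proportion with any AE is 1 − (1 + αm)^(−1/α). For α = 0.5:
- placebo, m = 3: 1 − 2.5^(−2) = 84%
- 20 L3, m = 6: 1 − 4^(−2) = 94%

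A doubled burden becomes a 10-point gap. For Poisson counts, the share of information on the log rate kept by an any-AE split is m/(e^m − 1): 77% at m = 0.5, 58% at 1, 31% at 2 and 16% at 3. More than half is lost only above m of about 1.26.

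Power was then simulated for the pairwise, uncorrected chi-squared test at successive cuts, and for a quasi-Poisson comparison. The latter uses the log ratio of mean counts, with SE √(φ(1/total₁ + 1/total₀)) and φ the Pearson dispersion.

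| Placebo mean | Dispersion | Chi-squared, any AE | Chi-squared, best cut | Rate comparison |
|---|---|---|---|---|
| 1 | 1.0 | 15% | 21% (≥3) | about 25% |
| 2 | 1.0 | 14% | about 25% (≥4 or ≥5) | 30% |
| 2 | 0.5 | 16% | 38% (≥4) | 50% |
| 3 | 0.5 | 10% | 43% (≥6) | 55% |

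Over the whole grid the ranges are about 1–24% (any AE), 20–60% (best cut) and 25–74% (rate comparison). Type I error of the rate comparison is 4–6%. The best cut moves from one row to another, so it cannot be picked without knowing the AE rates. These are pairwise figures; the plan's test spans three groups.

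**The case against.** Several points on the other side are sound.

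- **The test is not wholly misplaced.** AE number is one of three components. Completion of 24 months is already binary and suits a test of proportions, and a participant-level composite is a recognised design. A reader might infer that the planned test misses the endpoint altogether; the document does not support that.
- **The cut need not be any AE.** A reader might also infer that the test discards most of the information in the AE data. That holds only for a poorly placed cut with frequent events. The protocol expects abdominal symptoms during colonisation and itch at the inoculation site, grades reactions by severity and counts SAEs, so a severity-based rule fits its text at least as well.
- **The loss can be small.** With mean 2 and dispersion 1.0, a rank test on the counts has 26% power against 25% for chi-squared at the best cut.
- **Very low power figures need the wrong test.** With Fisher's exact test at any AE, means of 2 to 4 and dispersion 0.3 to 0.5, power is 0.2–7%. The plan names chi-squared, and larger dispersion is possible.
- **AE counts would still be seen.** Descriptive statistics cover all outcome measures, so a doubled burden would not be hidden.
- **A raw count is imperfect too.** It weights a mild itch like a severe event.

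These points limit the size of the problem but leave the mismatch in place. The Kaplan-Meier and Cox models rest on an event, safe progression, that is equally undefined, and time to an event is not a number of events. Descriptive summaries do not compare arms. A pass mark may exist in a fuller document, but the article does not merely omit detail: it names a test that does not fit the first component of its own outcome.

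**Conclusion.** The concern holds as a mismatch between the stated primary outcome and its stated test. The number of AEs relative to placebo has no between-group analysis, and the proportion that is tested depends on a rule given nowhere in the article. How much this costs is not known. Under the assumptions above, it runs from a few points of power at the best cut to nearly all of it at any AE with frequent events. In those scenarios the rate comparison had at least the power of every cut tried. The documents do not support a claim that most of the information is necessarily lost, because they give neither AE rates nor a cut.

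**What to change.** In Safety of infection, replace the single test with an analysis of each component:

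1. Compare the number of AEs per participant between 20 L3 and placebo by a negative-binomial or quasi-Poisson model with log follow-up time as offset, reported as a rate ratio with 95% CI. Do the same for 40 L3 against placebo as secondary.
2. Report SAEs, general health and completion of 24 months as separate components, using a test of proportions only for those that are binary.
3. If a composite proportion is kept, write its per-participant rule into the plan before unblinding.
4. Show AE counts by severity beside the rate ratio, because the raw count treats mild and severe events alike.

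The cost is a few sentences. AEs are already collected by structured questionnaire, and early terminations and withdrawals are recorded, so follow-up time is available. The price is a modelling assumption about overdispersion and, with 15 per arm, what may be a wide interval. That interval still shows which increases in AE rate the trial cannot exclude, which a non-significant chi-squared result does not.

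### The test named for the primary outcome compares all three arms, so its p-value does not isolate 20 L3 against placebo

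*Protocol article*

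**What the plan says.** Three places in the protocol article bear on this.

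- **Outcomes** sets the primary question on the lower dose: "The primary outcome measure will be the safety of experimental hookworm infection of otherwise healthy women and men with 20" L3 of the hookworm. The first secondary outcome in the same section is "safety/tolerability of the higher dose of 40" L3.
- **Table 1 (trial registration data set), primary outcome**, also names 20 L3. It gives a comparator for one component only, the adverse event count: "Number of reported adverse events (AEs), relative to placebo cohort". The other two components, general health and completion of 24 months, carry no stated comparator.
- **Safety of infection** (under Data processing and statistical analyses) says that the primary outcome, again named as the safety of 20 L3, will be tested by chi-squared for "any differences in the proportions satisfying the safety criteria at 24 months between the placebo, 20 x L3 and 40 x L3 groups".

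The same section adds Kaplan-Meier models and says that "Cox regression models will assess safe progression through the study". It states no contrast for either. It gives no pairwise follow-up to the chi-squared test, no order of testing, no significance level and no expected safety proportions.

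**The concern.** A chi-squared test across three groups asks whether any of the three proportions differ. It does not ask whether 20 L3 differs from placebo. The question and the test stand in one sentence of the article, and they do not match.

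This matters in two directions. If only 40 L3 does worse, the test named for the 20 L3 outcome can be significant although 20 L3 and placebo are the same. If 20 L3 does worse and 40 L3 lies between, the extra arm and extra degree of freedom can hide the 20 L3 excess.

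The first direction deserves attention because the section on randomisation and inoculation itself reports that adverse effects become more troublesome above 25 L3, and the 40 L3 total lies above that figure.

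This is not a detail left to an analysis plan. The article fixes both the test and the groups in it. An analysis plan that follows the article inherits the mismatch, and one that departs from it contradicts the published protocol.

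**Working it through.** **Inputs.** From the documents: 15 participants per arm (Sample size). Assumed, because the article does not give them: two-sided 5%, and the proportion failing the safety criteria in each arm.

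**The plan's own figure.** The 15 per arm comes from HOMA-IR, not from safety. It reproduces: (1.960 + 0.842) × √(2/15) = 1.023, the stated z-based effect size. The two-sample t-test has 80.0% power for 1.06 with 15 per group. No figure is given for the safety comparison, so there is none to reproduce.

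**Formulas.** Let a, b, c be the failures out of n = 15 on placebo, 20 L3 and 40 L3.

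- Three groups: p̄ = (a+b+c)/45, X² = Σ(o − 15p̄)² / [15p̄(1−p̄)], 2 df.
- 20 L3 against placebo: p̄ = (a+b)/30, X² = [(a−b)/15]² / [p̄(1−p̄)·2/15], 1 df.

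**Example 1: signal only from 40 L3.** Failures 1, 1, 7. p̄ = 9/45 = 0.20 and the expected count is 3. Σ = 4 + 4 + 16 = 24. X² = 24/(15 × 0.2 × 0.8) = 24/2.4 = 10.0, p = 0.007. For 20 L3 against placebo, a = b, so X² = 0 and p = 1.00.

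**Example 2: signal from 20 L3 blurred.** Failures 1, 6, 3. p̄ = 10/45 = 0.222 and the expected count is 3.33. Σ = 5.44 + 7.11 + 0.11 = 12.67. X² = 12.67/2.593 = 4.89, p = 0.087. For 20 L3 against placebo, p̄ = 7/30 and X² = 0.1111/0.02385 = 4.66, p = 0.031 (Fisher 0.080).

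**Rejection probabilities.** All 16 × 16 × 16 outcomes were enumerated with independent binomial weights, n = 15 per arm.

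*20 L3 equal to placebo, only 40 L3 worse:*

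| Failing, placebo/20 L3/40 L3 | Three-group test | 20 L3 v placebo, chi-squared |
|---|---|---|
| 10/10/20% | 0.09 | 0.025 |
| 20/20/30% | 0.09 | 0.050 |
| 20/20/40% | 0.23 | 0.050 |
| 10/10/30% | 0.27 | 0.025 |
| 20/20/50% | 0.45 | 0.050 |
| 10/10/40% | 0.52 | 0.025 |
| 20/20/60% | 0.68 | 0.050 |
| 10/10/50% | 0.76 | 0.025 |

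At 10/10/50%, the three-group test is significant while the direct test is not in 0.74 of trials. With all arms equal, the three-group test rejects in 0.035 (10%) or 0.043 (20%), so the excess above comes from 40 L3.

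*20 L3 truly worse than placebo:*

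| Failing, placebo/20 L3/40 L3 | Three-group test | 20 L3 v placebo, chi-squared | 20 L3 v placebo, Fisher |
|---|---|---|---|
| 10/50/30% | 0.60 | 0.73 | 0.54 |
| 20/60/40% | 0.52 | 0.63 | 0.45 |
| 10/50/50% | 0.71 | 0.73 | 0.54 |
| 10/50/10% | 0.76 | 0.73 | 0.54 |

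The power loss against the direct chi-squared appears when 40 L3 lies between the other two. It almost vanishes when both doses are equally harmful and reverses when 40 L3 equals placebo. Fisher's test has lower power than the three-group test in all four rows.

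**The case against.** The strongest case on the other side has four parts.

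1. *There is no decision rule.* A reader might infer that an excess confined to 40 L3 would be reported as a failed primary safety outcome for 20 L3. The article does not support that. It sets no significance level, no threshold and no link from p-value to a safety conclusion. It also promises descriptive statistics for all outcome measures, and if these are shown by arm, as is usual, the source of a difference would be visible. This stands and limits the harm to misattribution.

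2. *The comparator is less explicit than it looks.* The Outcomes section does not mention placebo, and Table 1 attaches it only to the adverse event count. That is correct. A placebo comparison for the other components is a fair inference from a placebo-controlled design, but an inference. Either way, a test that includes the secondary dose does not isolate 20 L3.

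3. *The large figures depend on assumed gaps.* A reader might take the text on doses above 25 L3 to mean that the 40 L3 arm is expected to fail. The article predicts no failure proportion, and it gives the 40 larvae as two inoculations of 20, eight weeks apart. So the whole range from 9% to 76% should be quoted, not its upper part.

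4. *Other analyses are named.* A Cox model with placebo as reference would yield a 20 L3 estimate, and pairwise follow-up of a three-arm test is common. But neither contrast is written, and the chi-squared is the only hypothesis test tied to the primary outcome. Unstated follow-up tests could be chosen after the data are seen. This lowers the severity but does not remove the mismatch.

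**Conclusion.** The point holds as a mismatch between the stated primary question and the stated primary test. When only 40 L3 is worse, the p-value named for the 20 L3 outcome is significant in roughly 9% to 76% of trials, against 2.5% to 5% for the direct chi-squared. The size within that range depends wholly on the assumed failure proportions, on two-sided 5%, and on 15 evaluable participants per arm.

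Masking of a real 20 L3 excess is a secondary argument. It arises in some patterns only (0.60 against 0.73 at 10/50/30%), and it depends on comparing chi-squared with chi-squared.

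This should be fixed. It is not more severe than that, because this small Phase 1b trial states no rule by which the test would decide whether 20 L3 is safe.

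**What to change.** Replace the sentence in Safety of infection with wording to this effect: *The primary comparison is 20 L3 against placebo, reported as the difference in the proportion meeting the safety criteria at 24 months, with an exact or score-type 95% confidence interval. If a p-value is given, it comes from an exact test. The same comparison of 40 L3 with placebo, and any test across the three groups, are secondary.*

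The interval method should be named because counts will be small: at 10% failure, 15 × 0.10 = 1.5 failures are expected per arm. An exact test costs power, as the Fisher column shows, which is a further reason to lead with the estimate and its interval. With 15 per arm, a non-significant result under either test is weak evidence of safety.

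If the Cox model is kept for safe progression, state that its contrast is also 20 L3 against placebo.

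The cost is a sentence or two in the protocol and the matching line of the analysis plan. No new data or participants are needed, and no dose or clinical rule changes.
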